### Protocol deviations

Deviations from this protocol will be recorded and disseminated as protocol deviations with classification of risk (minor/major).

### Missing data and robustness

Missing data will be investigated by producing tables that characterize survivors with missing data vs. survivors with information for each missing variable, as outlined in Supplemental Table 1. There may be missing data in many variables, so variables of interest will be assessed.

If survivors with missing data differ from survivors without missing data, it is assumed that data is missing not at random and multiple imputation may be redundant. Otherwise, multiple imputation may be used as a sensitivity analysis. Whether imputation can be used will be based on a judgment of the extent of patterns in missingness. All secondary outcomes will be assessed as cross tables with intervention, primary outcome, age, sex, marital status, and occupation. As a rule of thumb, differences should be less than 5% between survivors with and without missing data, but the total pattern will be considered.

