### Sample size

The sample size calculation for the present trial is based on a study by Moulaert et al. who evaluated the effectiveness of a rehabilitation intervention on health-related quality of life for OHCA survivors but reported exploratory finding for RTW after 1 year. In that study, 71% of the control group had returned to work after 1 year. We expect the intervention to increase this by 25% corresponding to a RTW rate of 88.8%. Using the formula for large-sample tests for proportions in a two-sample parallel design with a superiority margin of 10% and a power of 80%, 85 survivors are needed in each arm, 170 in total. Based on the sample size calculation and an expected 20% dropout rate, 107 OHCA survivors are needed in each study arm, 214 in total [42].

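### The missing-data rule reads differences on observed variables as missing not at random and sets imputation aside, and its 5% guide lies within sampling noise

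*Protocol article*

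**What the plan says.** The section Missing data and robustness in the protocol article sets a two-branch rule. First branch: if survivors with missing data differ from those without, "it is assumed that data is missing not at random and multiple imputation may be redundant". Second branch: "Otherwise, multiple imputation may be used as a sensitivity analysis".

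The comparison uses observed data: "All secondary outcomes will be assessed as cross tables with intervention, primary outcome, age, sex, marital status, and occupation". The size of difference that matters is given as "As a rule of thumb, differences should be less than 5% between survivors with and without missing data, but the total pattern will be considered". The decision keeps an element of discretion: "Whether imputation can be used will be based on a judgment of the extent of patterns in missingness".

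Three other sections bear on the consequences:

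- Secondary outcomes (statistical methods) plans generalized linear mixed-effects models for repeated measures, and also lists t-tests, Wilcoxon tests and chi-square tests.
- Definition of analysis adds complete-case and per-protocol analyses to intention to treat.
- Primary outcome takes labour market status from the DREAM register.

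**The concern.** The rule runs together two kinds of missingness that call for different handling. If people who drop out differ from those who stay in arm, age, sex, marital status, occupation or work status, then missingness is related to things that were measured. That is evidence against MCAR and is what MAR allows. MNAR means dependence on the unseen values themselves after conditioning on what was seen, and no cross table of observed variables can show that.

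So imputation is set aside in the case where conditioning on the observed predictors could remove bias. It is offered in the case where the data look close to MCAR and it has least to correct.

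The 5% guide adds to this. If chance alone usually produces a difference of that size in a trial this small, the guide will tend to point towards MNAR even when missingness is harmless. The choice is then left to a judgment made from tables that include arm and the primary outcome.

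**Working it through.** **Group sizes.** The Sample size section gives "an expected 20% dropout rate, 107 OHCA survivors are needed in each study arm, 214 in total", starting from 85 per arm. Check: 85 / (1 − 0.20) = 106.25, rounded up to 107; 2 × 107 = 214. This reproduces. At 20% missing, 0.20 × 214 = 42.8, so about 43 missing against 171 observed. The plan states no error rate for the 5% guide, so there is none to reproduce.

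**One binary characteristic, missingness completely at random.** The standard error of the difference in proportions is √[p(1−p)(1/43 + 1/171)], with 1/43 + 1/171 = 0.0291.

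- At p = 0.5: √(0.25 × 0.0291) = 0.085, or 8.5 points, and 1.96 × 8.53 = 16.7 points.
- A 5-point difference is therefore about 0.6 standard errors.

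Exact binomial probabilities of a difference of 5 points or more:

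| Prevalence | P(difference ≥ 5 points) |
|---|---|
| 0.1 | 0.333 |
| 0.2 or 0.8 | 0.469 |
| 0.3 or 0.7 | 0.528 |
| 0.5 | 0.541 |
| 0.888 | 0.358 |

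**At least one of the six screened variables.** The article gives no prevalences for these characteristics in the trial population, so two sets are assumed, with independence.

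- Set 0.5, 0.8, 0.5, 0.2, 0.3, 0.5: 1 − 0.459³ × 0.531² × 0.472 = 0.987.
- Low-variance set 0.5, 0.888, 0.1, 0.1, 0.1, 0.1: 1 − 0.459 × 0.642 × 0.667⁴ = 0.942.

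How this moves with the assumptions:

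- 10% missing (21 against 193): 99.8% and 98.7%.
- 30% missing (64 against 150): 98% and 89%.
- If the six behaved like only two independent variables (0.5 and 0.3): 1 − 0.459 × 0.472 = 0.78.
- With the first set and 20% missing, the rate falls to about 29% only near 2,000 participants and 2% near 5,000.

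The scale of the 5% is not stated; percentage points are assumed. Read as 5% of the observed proportion, the any-of-six rate exceeds 99.9%.

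**What setting imputation aside can and cannot cost.** An illustrative simulation used 107 per arm, about 21% missing, missingness driven only by arm and one observed covariate, and a true arm difference of 0.30. Over 4,000 runs the mean estimates were:

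| Analysis | Estimate |
|---|---|
| Cases with data, unadjusted | 0.59 |
| Cases with data, adjusted for the covariate | 0.30 |
| Imputation from arm and covariate | 0.30 |

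The bias arises when the variable that drives dropout is left out of the analysis. It disappears when that variable enters either the model or the imputation. A second illustration let the interim score drive dropout in one arm, with about 23% missing at the last visit. Case-only bias was −0.23, against −0.01 for a mixed model using both follow-up visits.

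**Where that leaves the planned analyses.** The primary model contains arm, age, sex, marital status and occupation. The adjusted secondary models contain age, sex, educational level and marital status, but not occupation or the primary outcome. Of the screened variables, those two are the ones that imputation could use and the secondary models do not.

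**The case against.** The strongest reply is that little depends on this rule. Parts of that stand.

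- **Imputation is not forbidden.** The text says it may be redundant, calls the 5% a rule of thumb and defers to the overall pattern. A reader might infer that imputation would be switched off by chance in about 97% of trials, since all of five assumed variables stay under 5 points only about 3% of the time. That treats a discretionary guide as a mechanical trigger, and the article does not support it. The discretion does not correct the direction of the rule, however.
- **The main secondary analysis is not case-only.** A reader might take a bias of about 0.2 SD, as seen in case-only simulations, to be the bias in the trial's secondary results. The planned mixed models, if fitted by likelihood to all available visits, handle MAR outcome dropout. Covariate-adjusted analysis of cases with data is also unbiased when missingness depends only on covariates in the model. The simple tests, the complete-case population and incomplete covariates remain exposed.
- **The primary outcome is largely untouched.** It comes from a register, and imputation is only a sensitivity analysis. A reader might suppose that the primary model's covariates come from questionnaires and are therefore prone to be missing; the article does not say so, and age and sex are stratification factors. Patient reports only supplement the primary analysis.
- **No MNAR analysis is named.** That may be left to the full statistical analysis plan, so its absence here is not an error.

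**Conclusion.** The rule is wrong as written: it takes departures from MCAR on observed variables as proof of MNAR, and it places imputation in the branch where it is least useful. The 5% guide does not separate signal from noise at this sample size. Chance exceeds it in about 33-54% of trials for one binary variable and in about 94-99% for at least one of six. Those figures rest on 20% missing, assumed prevalences, independence and a percentage-point reading; they describe how often the guide is exceeded, not how often imputation would be abandoned.

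The consequence is moderate. It concerns secondary questionnaire outcomes wherever case-only tests, complete-case populations or incomplete covariates are used, and information from occupation and work status that the secondary models leave out. The size of any bias in this trial cannot be derived from the article. The rule should be fixed, but the primary conclusion does not hang on it.

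**What to change.** Delete the statement that observed differences imply MNAR and make imputation redundant, and delete the 5% guide. In their place, state that:

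1. the main analyses assume MAR, and the secondary mixed models are fitted by likelihood to all available visits;
2. variables related to missingness go into the multiple imputation model, including arm, occupation, DREAM status and earlier scores, together with the analysis covariates;
3. that imputation is used whenever outcomes or covariates are missing outside the likelihood mixed models;
4. where MNAR is suspected, it is examined with a delta-adjusted sensitivity analysis rather than by dropping imputation.

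The tables comparing survivors with and without missing data can stay, as description and as a guide to the imputation model. The cost is a wording change and modest extra analysis, with no new data. The article commits to uploading a full statistical analysis plan before analysis, and the correction can be made there, with the change registered and justified as the Protocol amendments section requires.

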### Definition of analysis

Intention to treat, complete cases, and per protocol will be conducted for primary and secondary outcomes. Intention to treat is the sample of all survivors included who attended their first visit at the Center of Social Medicine. Complete case is the population with either a baseline assessment or assessment after 2 weeks and either a complete 6-month or 12-month assessment, for secondary end points to be derived. The per protocol population is the population of survivors with a rehabilitation plan including planned RTW interventions.

Sensitivity analysis will be conducted for the primary outcome on the following subgroups: blue collar vs. white collar, manual labour vs. non-manual, and doing several tasks at the same time vs. work concentrated on one issue at a time.

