### Outcomes

#### Primary outcome

Data for the primary outcome will be obtained from the national register on social transfer payments (DREAM) [20]. The DREAM register is a prospective register based on data from the Ministry of Employment, the Danish Education Registers, the Danish Civil Registration System (CPR registry), and the Danish Tax Authority. The register contains all citizens in Denmark, who have received one or more social transfer payments in the period from 1991 until today. The type of transfer payment is registered on a weekly basis, and the register is updated monthly.

The primary outcome of the clinical trial is labour market participation, defined as a dichotomized outcome, employment vs. on social transfer payment 12 months after hospital discharge.

This measure has been proposed as adequate and relevant measure for assessing employment prognosis following intervention on a similar group of patients [21]. Furthermore, data will be obtained by questionnaire on the degree of workload and comparable work tasks compared to pre-cardiac arrest. Hence, labour market participation 12 months after hospital discharge (employment vs. social transfer benefits (DREAM)) and labour market participation during the 12 months after hospital discharge (DREAM) will be analysed.

Sequence analysis and a multistate model analysis will be used to visualize how survivors change states during the follow-up time and to assess influences from covariates on transitions between stages.

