### Strategies to improve adherence

The feasibility of the intervention has been tested and the intervention refined based on the gained experiences. As the study is a pragmatic study based on an individual assessment of the survivors’ expressed needs, the intervention is expected to be relevant for all participants. However, due to the single centre set-up transport to and from the study site could be a limiting factor to adherence. However, financial compensation for transport costs was offered to the participants. Furthermore, the intervention is designed to include relatives, and hence, the acceptability is expected to be relatively high, and relatives are therefore expected to be supportive and thereby increase the possibility of higher adherence to the intervention.

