### Recruitment, assignment of interventions, sequence generation, and allocation concealment

We will recruit trial participants directly from the cardiology ward. A study nurse at the ward will approach eligible survivors and invite them to participate in the present study. Participants will be randomly assigned to either the intervention or the usual care group using a computer random generator, with a 1:1 allocation by using varying block sizes. The randomisation will be conducted using the RedCap randomization module and will be stratified on sex (M/F) and age. Allocation concealment will be ensured as the randomization module block sizes are unknown, and the allocation will be locked after randomization. Clinical staff at the departments will obtain informed consent and enroll the participants. A named study author ([name], [name], or [name]) will randomize participants, and the clinical staff at the departments will inform the participants about the allocation and start the intervention based on standard operating procedures. The CONSORT flow diagram is presented in Fig. 2.

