### Blinding

Due to the nature of the intervention, neither participants, outcome assessors, nor staff conducting the intervention can be blinded to allocation. Group allocation will be anonymized before the data will be analysed by the data analysis responsible investigator to ensure blinding.

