### Per protocol population

For survivors to be included in the per protocol analysis on the primary outcome, they should be classified as adherent to the intervention. Furthermore, to be included in the per protocol analysis for the secondary outcome, the first assessment timepoint and an assessment after 52 weeks are needed. No exclusion criteria will be imposed in relation to the usual care group.

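### The population called intention to treat requires attendance at a Center of Social Medicine visit, and no other listed set contains all randomised participants

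*Protocol article*

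**What the plan says.** Definition of analysis announces three sets: "Intention to treat, complete cases, and per protocol will be conducted for primary and secondary outcomes". The first is defined by attendance: "Intention to treat is the sample of all survivors included who attended their first visit at the Center of Social Medicine". Complete case, in the same section, requires an early assessment and a complete later one. Per protocol requires a rehabilitation plan with return-to-work interventions; the section Per protocol population instead requires adherence to the intervention.

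On the order of events, the section on recruitment and assignment says "We will recruit trial participants directly from the cardiology ward". Department staff obtain consent and enrol, a study author randomises, and then "the clinical staff at the departments will inform the participants about the allocation and start the intervention based on standard operating procedures". The Blinding section adds that "neither participants, outcome assessors, nor staff conducting the intervention can be blinded to allocation".

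The primary outcome, employment versus social transfer payment at 12 months, is taken from the national DREAM register (Primary outcome, under Outcomes). Participants who withdraw are asked whether register data not yet collected may still be used (Criteria for discontinuing the trial).

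**The concern.** Intention to treat preserves the comparison that randomisation created, because membership is settled by randomisation and by nothing that follows it. Here membership is settled by turning up at a centre, most naturally when the participant already knows the allocation.

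Attendance could plausibly be related to the outcome in either direction. The most impaired survivors may be unable to travel, and the quickest to recover may have no time or see no need. If attendance depends on arm as well, those who remain in the two arms are no longer comparable, and a superiority claim would rest on a selected comparison. The protocol itself sees a travel problem: "due to the single centre set-up transport to and from the study site could be a limiting factor to adherence". The exclusion also gains little, since a register outcome does not require a visit.

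**Working it through.** **Step 1. When does the visit occur, and for whom?** The recruitment section places enrolment, randomisation and disclosure of allocation with the cardiology departments and does not mention the Center of Social Medicine. The Center visit is therefore most naturally later than disclosure. This is an inference. The running text gives no date for the visit, and the schedule table, intervention figure and flow diagram could not be read in the text at hand. The Usual care section mentions an occupational therapist (depending on the MoCA score) and municipal rehabilitation, but no Center visit; it describes treatment, however, not study visits. Two cases remain:

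- Only the intervention arm attends. The rule then removes intervention non-attenders only or, read literally, leaves no controls.
- Both arms attend. The set is then a modified intention-to-treat set in which attendance can still differ by arm, because allocation is open.

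**Step 2. Is there an all-randomised set elsewhere?** Complete case depends on completed assessments. Per protocol depends on a rehabilitation plan or on adherence, and for that set "No exclusion criteria will be imposed in relation to the usual care group", so its selection acts on one arm. Neither is all-randomised.

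**Step 3. How large could the effect be?** The plan gives no figure for first-visit attendance, so this step is illustrative.

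Inputs from the Sample size section: 71% return to work in controls, and 107 randomised per arm (85/0.8 = 106.25, rounded up to 107). Nothing here depends on how the 85 was derived.

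Assumptions: no true effect (71% in both arms); exclusion in the intervention arm only; f = share of that arm excluded; q = return to work among those excluded.

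Rate among those retained = (0.71 − f·q)/(1 − f). The spurious difference is that rate minus 0.71.

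| f | q | Rate among retained | Difference (points) | Type I error |
|---|---|---|---|---|
| 5% | 50% | 0.685/0.95 = 0.721 | +1.1 | 5.4% |
| 10% | 50% | 0.660/0.90 = 0.733 | +2.3 | 6.5% |
| 20% | 50% | 0.610/0.80 = 0.7625 | +5.25 | 12.7% |
| 10% | 90% | 0.620/0.90 = 0.689 | −2.1 | 6.3% |
| 20% | 90% | 0.530/0.80 = 0.6625 | −4.75 | 11.0% |

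The last column is the rejection rate, in either direction, of an unadjusted two-sided 5% z-test with 107 controls and 107(1 − f) intervention participants. It stands in for the planned adjusted logistic model. For f = 20%, q = 50%: 85.6 are retained and the pooled rate is (107 × 0.71 + 85.6 × 0.7625)/192.6 = 0.733. The standard error is 0.0641 under the null and 0.0636 unpooled. The upper tail is 1 − Φ((1.96 × 0.0641 − 0.0525)/0.0636) ≈ 0.125 and the lower tail about 0.003, together 12.7%.

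**Step 4. If both arms attend.** With the same f and q in each arm, the difference is zero. Equal numbers lost are not enough, though. If each arm loses 10%, with q = 50% in the intervention arm and 71% among controls, the control rate stays at (0.71 − 0.071)/0.90 = 0.71 and the difference is again +2.3 points. If q = 50% in both arms but 10% are lost from intervention and 5% from control, it is 73.3 − 72.1 = +1.2 points.

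**The case against.** The strongest reply is that the mechanism is inferred. The text neither dates the visit nor says which arm attends. A footnote to the schedule table marks some items as for the intervention group only, which suggests that others are common to both arms. If both arms attend a shared first visit and few miss it, the bias may be a point or less. This stands, and it limits what can be said about size. It does not repair a definition that makes membership depend on attendance.

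Several stronger readings are tempting but not supported:

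- *The control arm will be empty.* A reader might infer this because the Usual care section mentions no Center visit. Silence in a description of treatment does not show that controls never attend.
- *The protocol confirms one-sided exclusion.* The statement that usual care faces no exclusions concerns the per-protocol set only.
- *Travel will keep participants away.* The remark on transport concerns adherence to the intervention, and the next sentence says that transport costs were compensated.
- *The bias could reach the plan's 10% superiority threshold.* It could if 20% were excluded with 30% return to work (0.65/0.80 = 0.8125, or +10.25 points), but the documents support neither value. The plan's 20% is expected dropout overall, not first-visit non-attendance in one arm.
- *DREAM classifies every randomised person.* The statistical section on the primary outcome says that questionnaires supplement the register for the self-employed and some others, and that retirement on a private pension is not registered.
- *The flawed set is the declared primary analysis.* The protocol names no deciding set, and the full analysis plan is not at hand. The point is that none of the three sets offered is all-randomised.

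**Conclusion.** The point holds in this form: the protocol gives the name intention to treat to a set conditioned on a visit that most naturally follows open allocation, and it lists no set of all randomised participants. As written, no planned primary comparison is protected by randomisation. That conclusion rests on the definition itself and on the order of events in the recruitment section.

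Neither the direction nor the size of the bias can be established from the document. Roughly +1 to +5 points, or −5 in the opposite scenario, is what one-sided exclusion of 5% to 20% would do under the assumed return-to-work rates. Should a schedule or figure show that the visit precedes randomisation, the bias concern would largely fall away, but the definition would still need rewording to say so. Correction is needed before analysis, because the validity of the main result depends on it.

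**What to change.** Replace the definition along these lines: *Intention to treat comprises all randomised participants, analysed in the arm to which they were allocated, whether or not they attended any visit. The primary outcome is taken from DREAM for all of them except those who refuse use of register data.* State that this set decides the primary outcome. Retain the attendance-based set, if wanted, as a supportive analysis under another name such as modified intention to treat, and say when the visit takes place and which arm attends.

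The cost is a few sentences, recorded through the route in Protocol amendments; no additional visits are needed. There is one small downside. Participants without questionnaires will be classified from DREAM alone, so those whose status it does not capture, such as the self-employed or those on private pensions, may be misclassified. A stated rule for register-only participants, with a sensitivity analysis that classifies the uncertain cases both ways, would address this.
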